## **6.9 Changes from Protocol**

## EVG001SAH Statistical Analysis Plan

1. The use of modelling rather than hypothesis testing where possible to allow more powerful analysis through inclusion of covariates and the generation of treatment estimates with confidence intervals.
2. Refinement of the per-protocol definition to consist of patients who receive at least 10 doses of randomised treatment within the first 7 days post-ictus and to exclude patients with potential dispensing errors.
3. Clarification that mRS and GOSE at 90 days are key secondary endpoints

## 7 Presentation of Data

This section describes the presentation of the results, supporting displays will be detailed in a separate document.

### *General Information*

All continuous data will be presented as means, standard deviation, minimum, maximum, median, lower quartile, and upper quartile as well as number of observations for both actual values and change from baseline data. Loge-transformed data, PK and TCD, will be summarised using geometric mean, coefficient of variation (CV), minimum, maximum, median, lower quartile, and upper quartile as well as number of observations. CV will be calculated as  $\sqrt{\exp(\sigma^2)-1}$ , where sigma is the standard deviation of the loge-transformed data. All descriptive summaries will be displayed to one more decimal place than actually measured. All categorical data will be presented in contingency tables as frequencies and percentages and the denominator will be the number of patients available in the relevant population who have data recorded.

All the tables will be summarised using the treatment arm allocation (SFX-01, Placebo), day and time post ictus or dosing as appropriate. Patients will be assigned to time windows as described in Section 5.15. Any assessments not assigned to time-windows, as other measurements are closer, will be flagged in the appropriate supporting listings.

All demographic summaries will be produced for both the ITT and PP populations according to treatment arm (SFX-01, Placebo). Summaries of TCD, mRS and GOSE data will also be produced for both the ITT and PP populations according to treatment arm (SFX-01, Placebo). Other secondary efficacy endpoints will be produced for only the PP population. Safety summaries and pharmacokinetic data reported outside of the sub-study will be produced for the Safety population and non-compartmental PK data from the sub-study will be summarised for the Sub-Study population only.

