### 4.1 Population Definitions

Four patient populations will provide the basis for all statistical analyses and data presentations.

**Per Protocol (PP) population:** This will consist of all patients who receive at least 10 doses of randomised treatment within the first 7 days of the first dose of study medication. However, there were nine patients (014, 015, 016, 017, 020, 021, 032, 033, 034) who were either known to have had (n=2), potentially had (n=3), or were associated with patients who had (n=4), a discrepancy in dispensing of randomised therapy, these patients will be excluded from the PP population.

**Intent-To-Treat (ITT) population:** All randomised patients who receive at least one dose of study medication. This population will include the nine patients excluded from the PP population due to possible errors in dispensing.

The primary population for efficacy endpoints will be the PP population with select efficacy endpoints also analysed in the ITT population (see Section 6.2)

**Safety population:** All randomised patients who have taken at least one dose of study medication including the nine patients excluded from the PP population due to possible errors in dispensing. This population will be applied to all safety endpoints and pharmacokinetic data recorded in all patients. The safety population will be identical to the ITT population if all patients dosed have efficacy data recorded.

**PK Sub-Study population:** A group of up to 12 patients fitted with an EVD as part of their normal treatment are to be selected for the pharmacokinetic sub-study.

Given the early stage of development, the PP population is of primary interest and all patients will be analysed according to the treatment they actually receive in all populations. For the ITT population, if due to dispensing errors it is known patients received a mixture of SFX-01 and placebo capsules, they will be assigned to the arm for which they received medication for the majority of time.

In addition, clinically important protocol violations will be identified in a blinded manner and then summarised and listed in the clinical study report (CSR).

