### ***Adverse Events (AEs)***

MedDRA coded events will be summarized by treatment arm and overall. The number of patients reporting adverse events will be presented according to the coded Preferred Term and System Organ Class (SOC).

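### Sections 7 and 4.1 of the SAP can put the same patient in different table columns (treatment allocated versus treatment received), and the mixed-capsule rule is worded for ITT only although the Safety population holds the same patients

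*SAP*

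**What the plan says.** Section 4.1 of the SAP gives one general rule: "all patients will be analysed according to the treatment they actually receive in all populations". It then turns to patients who took both products, and the scope it sets for that case is "For the ITT population, if due to dispensing errors it is known patients received a mixture of SFX-01 and placebo capsules". The classification it gives such patients is by exposure: "they will be assigned to the arm for which they received medication for the majority of time".

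The same section explains why this matters here. Nine patients are named "who were either known to have had (n=2), potentially had (n=3), or were associated with patients who had (n=4), a discrepancy in dispensing". They are left out of the PP population but kept in ITT, and the Safety population is defined as "All randomised patients who have taken at least one dose of study medication including the nine patients excluded from the PP population". No mixed-exposure rule is given for Safety.

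Section 7, General Information, then says: "All the tables will be summarised using the treatment arm allocation (SFX-01, Placebo". The paragraph after next adds that "Safety summaries and pharmacokinetic data reported outside of the sub-study will be produced for the Safety population", without a separate column rule. The Adverse Events text says only "MedDRA coded events will be summarized by treatment arm and overall", and the Deaths and Laboratory Safety Assessments texts also refer just to treatment arm. Randomised and received treatment are explicitly separated only under Randomisation, Dosing And Drug Accountability, and there only in listings.

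**The concern.** Allocation and receipt are different things, and in this trial they are known or suspected to have diverged for some patients. Read literally, Section 7 puts such a patient in the allocated column, and Section 4.1 puts the same patient in the received column. The SAP does not say which section takes precedence.

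There is a second gap even if Section 4.1 governs. Treatment received does not by itself classify a patient who took both products. The only tie-break is worded for ITT.

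Safety is the first primary objective listed in Section 2, and the safety results in Section 7 are descriptive summaries by arm, so no model offsets a wrong column. The ITT summaries of TCD, mRS and GOSE are also tables under Section 7, so they could show arm sizes that differ from the as-treated ITT models. The Day 7 SFN concentrations are summarised for the SFX-01 group only, so the column rule also decides who enters that table.

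**Working it through.** **Step 1: which patients.** Section 4.1 gives 2 known + 3 potential + 4 associated = 9, which matches its stated nine.

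**Step 2: the rules side by side.**

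| Tables | Section 4.1 | Section 7 | Rule for known mixed exposure |
|---|---|---|---|
| PP | received | allocation | not needed for the nine, who are excluded |
| ITT (TCD, mRS, GOSE, demographics) | received | allocation | majority of time |
| Safety (adverse events, deaths, laboratory) | received | allocation | none stated |

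The rules agree wherever received equals allocated. They diverge only for patients with an actual discrepancy: 2 on what is known, 5 if every potential case is real, and 9 only if the associated patients were affected too.

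**Step 3: ceiling on the effect.** Section 3.1 gives 90 evaluable patients out of up to 120. The SAP states no allocation ratio, so 1:1 is assumed, giving 90/2 = 45 to 120/2 = 60 per arm. The most that k misfiled patients can move one arm's event rate is about k / arm size:

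| k | 45 per arm | 60 per arm |
|---|---|---|
| 1 | 1/45 = 2.2% | 1/60 = 1.7% |
| 2 | 2/45 = 4.4% | 2/60 = 3.3% |
| 5 | 5/45 = 11.1% | 5/60 = 8.3% |
| 9 | 9/45 = 20.0% | 9/60 = 15.0% |

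If the smaller arm instead held one third of 120 (40 patients), the figures for k = 1, 2, 5 and 9 would be 2.5%, 5.0%, 12.5% and 22.5%. All of these are ceilings. They are reached only if every misfiled patient has the event and all are misfiled the same way.

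**Step 4: a more typical size.** Assume, for illustration only, true event rates of 30% on SFX-01 and 15% on placebo, with 60 per column. If k patients in the placebo column had in fact taken SFX-01, that column reads [(60 − k) × 0.15 + k × 0.30] / 60:

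- k = 2: (8.70 + 0.60)/60 = 15.5%; the difference falls from 15.0 to 14.5 points.
- k = 5: (8.25 + 1.50)/60 = 16.25%; the difference is 13.75 points.
- k = 9: (7.65 + 2.70)/60 = 17.25%; the difference is 12.75 points.

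The reverse error is equally possible. With 2 placebo-treated patients in the SFX-01 column, that column reads (58 × 0.30 + 2 × 0.15)/60 = 29.5%, and the difference is again 14.5 points.

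**The case against.** The strongest reply is that Section 7 is only about presentation and that its phrase merely names the two column labels. Section 4.1 is explicit for every population and is the natural governing rule. Where the SAP means randomised treatment it says so, as in the dosing listings. This is a fair reading and may well be what was intended. What remains is that the SAP states no precedence and that Section 7 is where the tables are specified. At least one table there, disposition, does use the number randomised as its denominator, so the allocation reading is not far-fetched.

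A second reply is that ITT and Safety are almost the same patients, so a programmer would carry the majority rule across. That is likely, but the SAP does not say it.

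A third reply is that the affected patients are visible anyway: the nine are in the violations summary, their intended and actual treatment is listed by day, and serious events are listed by patient. This limits the harm, though listings do not correct a summary rate.

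Three stronger readings are tempting but unsupported:

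- **That SFX-01 events will be hidden under placebo.** The SAP does not say which way any discrepancy ran, nor how many patients took both products.
- **That only safety tables are touched because efficacy is compared as randomised.** Section 4.1 applies treatment received to ITT as well, so no as-randomised efficacy comparison is planned, and the conflict reaches the ITT summaries.
- **That the majority rule is wrong for safety.** Counting any exposure under the active arm is a common convention, but nothing in the SAP requires it.

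**Conclusion.** The inconsistency is real and should be reconciled. Two stated rules can give different columns for the same patient in the safety tables and the ITT summaries, and known mixed exposure has no stated rule in the Safety population. The PP tables are not affected by the nine flagged patients, who are excluded from them.

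The size is small: 2 patients on what is known, 5 with the potential cases, 9 at the outside. Each misfiled patient with an event moves an arm's rate by at most about 1.7 to 2.2 percentage points, under an assumed 1:1 allocation and 45 to 60 per arm. The shift in a common event would typically be much smaller, while for a rare serious event a single case can matter. The documents do not establish the direction of misfiling, and they do not show that the safety tables will in fact be built by allocation.

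**What to change.** 1. In Section 7, General Information, replace the reference to treatment arm allocation with the treatment arm as assigned for the relevant population in Section 4.1. This settles the ITT summaries as well as the safety tables, as treated, and the change should say so openly.
2. In Section 4.1, state before unblinding how a patient known to have received both products is classified in the Safety population. One option is to count any known SFX-01 exposure under SFX-01. Another is to extend the majority rule explicitly, accepting that a patient with mostly placebo and some SFX-01 would then count as placebo.
3. Footnote these patients in the adverse event tables.

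The cost is a few sentences and a footnote, with no new data or analysis. Under the any-exposure option, a patient who took mostly placebo may sit in the SFX-01 column and dilute it slightly. A rule limited to known exposure leaves the potential cases to the listings.

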### *Data presentations*

#### *Disposition*

A categorical summary of patient status detailing the number and percentage of: Screened, Randomized, Treated, Died, Completed will be produced by treatment arm. The denominator for percentages will be the number randomized so no percentage will be presented for the Screened row. This summary will be repeated for the patients in the PK sub-study. The number and percentage of subjects in each patient population (PP, ITT, Safety, PK) will also be given as well as the number of patients who have an EVD sited. Amongst patients who did not complete the study, the reason for withdrawal will also be summarised together with a cumulative incidence plot of time to withdrawal by treatment arm produced for both the PP and ITT populations.

#### *Major Protocol Violations And Deviations*

Major violations are to be summarised by treatment arm (SFX-01, Placebo) and overall for all patients and will include the nine patients associated with potential dispensing errors. The number of patients not meeting all inclusion and exclusion criteria will be summarised by treatment arm along with the reason. Supporting listings for both violations and deviations will be included which identify patient, treatment arm and the assigned population.

***Qualifying Evaluations (Surgery, Eligibility And Screening Procedures)***

Dates and times of all qualifying evaluations will be listed as: Onset of Ictus, Surgery (plus WFNS and any Triple H Therapy for Cerebral Vasospasm), Eligibility, Investigator Consent, Randomisation and Dosing. Other reported dates included: Discharge, MRI at follow up and End Of Study (EOS).

The time between Ictus and the patient receiving their first dose of randomized medication will be summarized for both the ITT and PP populations by treatment arm.

***Surgery Details***

Surgery details will be summarised for the ITT and PP population by treatment arm. Type of scan (CT/MRI), Angiographic assessment performed (CTA/ DSA/MRA), Fisher grading (No haemorrhage, SAH <1mm, SAH>1 mm, SAH any thickness with IV haemorrhage or parenchymal extension) and Surgical procedure (Coiling/Clipping), Triple H therapy for Cerebral Vasospasm (Yes/No) and WFNS (Grading I, II, III, IV, V).

***Eligibility And Screening Procedures***

Demographic data will be summarised for the ITT and PP population by treatment arm which will include a summary of the data recorded on aneurysm location and whether the patient developed a secondary bleed prior to randomisation. Medical History, Physical Examination, Pregnancy Test (if applicable) and Prior Medications will be summarised for the Safety population by treatment arm.

***Concomitant Medications***

All medications taken after the start of treatment are summarised according to WHODD ATC categorised through to level 4.

***Randomisation, Dosing And Drug Accountability***

All patient randomisation details will be listed indicating the treatment randomised and the treatment actually received. Any miss-randomisations will be flagged. In particular, the intended and actual treatment received on each day for the nine patients associated with potential dispensing errors will be listed.

Exposure to study drug will be described by summarising the dosing duration (date of last dose – date of first dose +1), total number of doses given and compliance ( $100 \times \text{total number of doses given} / [2 \times \text{dosing duration}]$ ) by treatment arm for both the PP and Safety populations. Individual details will be listed.

***TCD***

The maximum post-dose MCA mean flow velocity and the corresponding baseline value (see Section 5.1) will be summarised according to treatment arm (SFX-01, Placebo) for both the PP and ITT populations. The number of patients who have data imputed at baseline will also be summarised by treatment arm. In addition, the baseline values will be split according to whether they occurred before dosing, on Day1 and Day 2 and summarised by treatment arm.

Results of the statistical analysis will be presented as described in Section 6.4. A graphical presentation of the treatment effects and lsmeans over time will be produced using the results of the MMRM analysis.

***Glasgow Coma Score (GCS)***

## EVG001SAH Statistical Analysis Plan

The GCS daily scores (except Baseline) will be summarised as continuous data for both the both the best and worst daily score and for both the PP and ITT populations. Patients will be grouped into time windows as Days 3-4, 5-6, 7-9, 10-14, 15-21, 22-28.

### ***Secondary Efficacy Endpoints***

For mRS, CLCE-24, SAHOT and GOSE the percentage and cumulative percentage (best to worst score) of patients in each category will be summarised by treatment arm. SF-36 and BICRO-39 will be summarised as continuous data by treatment arm. The number and percentage patients with DCI, new cerebral infarct and institution of triple H therapy will be summarised by treatment arm together with a cumulative incidence plot displaying the time to each of these events across patients by treatment arm. A Kaplan-Meier (KM) curve of the length of acute hospital stay, will be presented along with an associated table presenting the 25th, 50th (median) and 75th percentiles derived from the KM curve. Discharge location will be summarised by treatment arm.

The results of the statistical analyses of all secondary endpoints will be presented as described in Section 6.5. Specified missing data diagnostics will also be presented by treatment arm as necessary as described in Section 6.7. Subgroup analyses will be presented as described in Section 6.8.

### ***Pharmacokinetic Endpoints***

The results of the analysis of blood HP and MDA concentrations at Day 7 and 28 and CSF HP and MDA concentrations at Day 7 will be presented as described in Section 6.6. The blood and CSF HP and MDA concentrations will be summarised by treatment arm at all timepoints noting that EVD patients have concentrations recorded at extra timepoints. For timepoints in common to both EVD and non-EVD patients data will be pooled across groups as well as presenting the data split by the use of an EVD.

For patients in the sub-study, the derived PK parameters in both CSF and blood will be summarised as described for loge-transformed data except for Tmax where the geometric mean and CV will not be calculated and median presented. Supporting graphical displays of individual and mean profiles will be produced by sampling day.

Individual SFN and SFN metabolite concentrations recorded on Day 7 and any concentrations recorded in the sub-study for patients outside of the sub-study using the summary measures described for loge-transformed data pooled across EVD and non-EVD groups. If <50% of concentrations are below the lower limit of quantification (LOQ) then data will be summarised substituting the LOQ in the calculation of the geometric mean and CV, otherwise these two parameters will not be presented. The median, LQ and UQ will be displayed as 'NQ' if those statistics correspond to a value below the LOQ. These summaries will only be produced for the SFX-01 group.

Note proteomic and genetic data will not be summarised as part of the CSR.

### ***Adverse Events (AEs)***

MedDRA coded events will be summarized by treatment arm and overall. The number of patients reporting adverse events will be presented according to the coded Preferred Term and System Organ Class (SOC).

## EVG001SAH Statistical Analysis Plan

An overview table of the number and percentage of patients with any Pre-Treatment Adverse Event (PTAE), TEAEs, Deaths, Serious TEAEs, All Serious AEs, TEAEs leading to discontinuation, maximum severity of TEAEs and Drug-Related TEAEs will be presented as a categorical summary according to treatment arm and overall. In the maximum severity row, patients will be counted once according to the worst severity categorized as missing/mild/moderate/severe/life threatening.

The following summarized of AEs will be produced:

- number and percentage of patients with at least one PTAE by Preferred term
- number and percentage of patients with at least one TEAE by Preferred term
- number and percentage of patients with at least one TEAE by Preferred term by maximum severity
- number and percentage of patients with at least one TEAE by Preferred term that is related to study drug
- number and percentage of patients with at least one TEAE by Preferred term that is serious
- number and percentage of patients with at least one adverse event that is serious, to include any serious AEs that occurred prior to dosing with study medication
- number and percentage of patients with at least one TEAE by Preferred term that lead to discontinuation of treatment corresponding to events where action taken with study treatment is 'Permanently discontinued'

In each table events will be grouped according to SOC and within each SOC events will be presented in order of decreasing frequency. The SOC row will present the number of patients with at least one TEAE within that SOC for the subset of events being summarized.

Serious TEAEs will be listed by patient and treatment arm, indicating the name of the AE, PT and SOC, together with details of the start and end dates, event duration (days) and maximum intensity. Additionally, the relation to study drug, action taken, outcome and the date of the first dose of study drug will also be displayed.

### ***Deaths***

All deaths during the study will be summarised by treatment arm (from EOS form). Details will also be listings. A KM plot of time to death measured from the date of ictus will be presented by treatment arm. Patients alive will be censored at the visit date completed for the End of Study CRF.

### ***Laboratory Safety Assessments***

Safety blood including lipid and coagulation tests performed throughout the study will be summarised as continuous variables by visit and treatment arm. Both actual values and change from baseline will be summarised. In addition, changes from baseline will displayed on a box-plot by visit and treatment arm for each parameter. Clinically significant findings for each parameter will be summarised in a shift-table by treatment arm, where the clinical significance of values recorded within 48h of ictus will determine the row and whether the patient has any later value recorded that is clinically significant will determine the column. Percentages will use the total number of patients in each row as a denominator. Corresponding shift tables will be produced for urine sample parameters.

EVG001SAH Statistical Analysis Plan

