### *Statistical Analysis Plan:*

A Phase II Safety, Tolerability, Pharmacokinetic and Pharmacodynamic Study of SFX-01 in Subarachnoid Haemorrhage, with exploratory efficacy evaluations. The study is a randomised, double-blind, parallel-group design comparing SFX-01 (300 mg) taken orally as capsules or as a suspension via a nasogastric tube (NG) twice-daily for up to 28 days versus placebo in 90 patients who have had SAH and present within 48 hours of ictus.

|                            |                                                                        |
|----------------------------|------------------------------------------------------------------------|
| Sponsor:                   | Evgen Pharma plc                                                       |
|                            | [name]
[name]
Liverpool
[name] |
| Author &
Qualifications | [name] M.Sc. C.Stat.                                             |

|                 |                  |
|-----------------|------------------|
| Document Date:  | 04 February 2019 |
| Version/Status: | Final            |

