### **5.13 Safety Data**

Recording of AEs starts from informed consent and continues until at least 30 days post last dose. The definition of AEs and SAEs are given in the protocol.

Adverse events starting on or after the first treatment dose are therefore defined as Treatment Emergent Adverse Events (TEAEs). Any AE that starts more than 30 days past last dose and is considered to be at least possibly related to study treatment should also be defined as a TEAE. Any event starting before the first dose of study drug is identified as a Pre-Treatment Adverse Event (PTAE). Any event starting before the first dose of study drug that subsequently worsens is also be defined as a TEAE.

All events are coded using the MedDRA dictionary. The actual description of the AE is matched, as closely as possible, with the Lower Level Term in the dictionary.

All AEs are classified as described in Table 10.

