## EVG001SAH Statistical Analysis Plan

Drug related events will be defined as ones whose relationship is given as certain, probable or possible. Any events with missing relationship to study drug will be tabulated as related. Any events with missing intensity will be tabulated in a separate category. If a patient has an AE which changes in severity this will be recorded as a separate occurrence of the same event. Serious adverse events (SAEs) are classified as described in the protocol. If a patient has more than one occurrence of the same AE and at least one is considered drug-related, the patient will be included as having a drug-related AE for that AE preferred term. Similarly, if a patient has more than one occurrence of the same AE and they have different severities, they will be summarised at the worst severity for that AE preferred term.

When summarising the time to onset of an AE the day of first dose will be used throughout as a reference point. If only a month is provided for date of onset, a conservative approach will be followed and events will be assumed to start at max(date of first dose, first day of the month). Likewise, if only a month is provided for the end date, the event will be assumed to have resolved at min(last date of month, date of onset for a new occurrence of the same AE for that patient).

For laboratory data all numeric blood results are classified by the investigator as Clinically Significant / Not Clinically Significant. All categorical urine results are classified as Clinically Significant (Yes / No). All blood and urine samples taken for safety evaluations are assayed by the local laboratory at each hospital. Data will be pooled across centres and summarised by treatment arm despite any differences in reference ranges.

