## **6.8 Subgroup analyses**

Subgroup analyses will be performed for maximum post-dose MCA mean flow velocity, mRS at 90 days and GOSE at 90 days for the following variables: centre, WFNS score (1-3 v 4-5), Fisher grade, time from ictus (<24h, 24-48h, >48h), Age group ( $\leq 49$ , 50-59,  $\geq 60$ ), gender, surgical procedure (coiling, clipping, not done), location of aneurysm (anterior, posterior), main vessel of aneurysm (anterior, middle, internal, vertebrobasilar) and whether the patient developed a secondary bleed prior to randomisation. Additionally, a subgroup analysis of the primary TCD endpoint will be performed by baseline value split according to quartiles. Results will not be presented for any subgroup level that contains fewer than 10 patients.

Data will be analysed separately for each level of the subgroup. For the primary TCD endpoint, the ANOVA model will be re-run and the treatment effect and associated 95% confidence intervals presented. For mRS and GOSE at 90 days, the logistic regression model will be performed within each level of the subgroup with the odds ratio and associated 95% confidence intervals presented. Results from all subgroups will be presented in a forest plot for each endpoint separately.

If there is evidence of heterogeneity of the treatment effect amongst subgroups the following tests will be performed:

1. A treatment-by-subgroup interaction term will be added to a model containing the terms included in the primary analysis model together with the main effect of the subgroup if not already included in the model. The p-value for the change in model fit by adding the interaction term will be presented
2. A test of the collective heterogeneity amongst subgroups will be performed. This will be achieved by comparing a base model including treatment and all main effects of subgroups with a model containing all two-way interactions of treatment and subgroup. The p-value for the change in model fit by adding all of the interaction terms simultaneously will be presented and described as a global interaction test.

Age will be fitted as a continuous covariate in the interaction tests.

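### The laboratory shift tables set baseline status by 48 h from ictus and ignore first dose, so an abnormality arising on drug before 48 h can be filed as baseline

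*SAP*

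**What the plan says.** SAP Section 7, Laboratory Safety Assessments, plans a shift table for each blood parameter and corresponding tables for urine. The row rule reads: "where the clinical significance of values recorded within 48h of ictus will determine the row". The column rule reads: "whether the patient has any later value recorded that is clinically significant will determine the column". On denominators: "Percentages will use the total number of patients in each row as a denominator". The paragraph does not mention first dose and gives no rule for a patient with several values inside the 48 h window.

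The same paragraph plans continuous summaries and box-plots: "Both actual values and change from baseline will be summarised". The SAP does not define baseline for these laboratory summaries.

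For adverse events, Section 5.13 uses first dose: "Adverse events starting on or after the first treatment dose are therefore defined as Treatment Emergent Adverse Events (TEAEs". It also says: "When summarising the time to onset of an AE the day of first dose will be used throughout as a reference point".

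On timing, the study title on the SAP's opening page describes patients "who have had SAH and present within 48 hours of ictus".

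**The concern.** A shift table is read as status before treatment against status on treatment. Here the dividing line is a clock started by the haemorrhage. If a patient is dosed before that clock reaches 48 h, a safety sample taken after the dose but before 48 h falls on the baseline side. A clinically significant result that first appears in that sample is then not shown as a change from not significant to significant.

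Two features make this more than wording. First, if the same abnormality is reported as an adverse event, it is treatment-emergent in the adverse event tables and a baseline abnormality in the shift table. Second, the SAP recognises the problem elsewhere. Section 6.4 says many TCD baselines will have been recorded shortly after dosing, and Section 7 (TCD) splits them into before dosing, Day 1 and Day 2. Section 6.6 splits baseline HP and MDA into pre-dose, within 24 h and 24 to 48 h after dosing. Both also have a fallback analysis if an early effect is seen. The safety laboratory tables have neither the split nor the fallback.

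At stake is the planned display of clinically significant laboratory change in a trial whose first-listed primary objective (Section 2) is safety. An early abnormality caused by SFX-01 would be lost from the SFX-01 arm with no matching loss on placebo.

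**Working it through.** The plan gives no figure to reproduce. The check compares the two dividing lines and then shows what misfiling does to a row percentage.

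**1. Interval filed on the wrong side.** Let h be the time of first dose in hours after ictus. For h < 48, the on-drug time counted as baseline is 48 − h.

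| h | 48 − h |
|---|---|
| 12 | 36 h |
| 20 | 28 h |
| 24 | 24 h |
| 36 | 12 h |

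The 48 h rule and a first-dose rule give the same table if h = 48, or if no safety sample falls between the two lines.

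**2. Effect on the row percentage.** Assumed, not from the SAP: 45 patients in an arm, all with a pre-dose sample; 5 clinically significant before first dose; 8 first significant on drug. Assume also that a significant value inside the window puts the patient in the significant row.

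- Split at first dose: the not-significant row holds 45 − 5 = 40, and the emergent rate is 8/40 = 20.0%.
- Split at 48 h from ictus, with k of the 8 first abnormal on drug before 48 h: the rate is (8 − k)/(40 − k).

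| k | Rate |
|---|---|
| 0 | 8/40 = 20.0% |
| 2 | 6/38 = 15.8% |
| 4 | 4/36 = 11.1% |
| 6 | 2/34 = 5.9% |
| 8 | 0/32 = 0% |

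The cell and its denominator both shrink because percentages are taken on row totals.

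**3. Dependence on the missing rule for several values.** Suppose instead that the first value in the window sets the row, and that value is pre-dose and normal. The patient stays in the not-significant row. On the plain reading, though, an on-drug value before 48 h is not a later value and cannot set the column. If the abnormality does not recur after 48 h, the rate is (8 − k)/40: 15.0% for k = 2, 10.0% for k = 4, 5.0% for k = 6. If it persists past 48 h it is counted correctly. So the first-value rule removes only part of the problem, and the SAP does not state that rule.

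**4. The other direction.** For h > 48, pre-dose values between 48 h and h would count as later (12 h at h = 60). This needs a first dose after 48 h and a sample in that gap. The only hint is the Section 6.8 subgroup "time from ictus (<24h, 24-48h, >48h", and that section does not say whether the interval ends at presentation, randomisation or dose.

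**The case against.** The strongest reply is that the safety sampling schedule is not in this document. Section 5.1 uses the same 48 h limit for the initial TCD reading, so in the laboratory paragraph it may simply label the first visit. If that visit has one safety sample, always taken before dosing, the 48 h rule and a first-dose rule give identical tables. This stands as a limit on size: how many patients are affected cannot be known from the SAP. It does not rescue the rule, which would then work only by an unstated feature of the schedule, while the SAP expects early TCD and HP/MDA values to be post-dose in some patients.

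It is also fair to say that the tables are descriptive and that the adverse event tables still run from first dose. Blood results are also shown by visit, and an early drug effect moved into the significant row would show as an imbalance in row totals between arms. All of that holds and keeps the point modest.

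A reader might infer two stronger things:

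- **That the rule errs in both directions.** The SAP does not establish that first dose can fall after 48 h, so pre-dose values counted as later remain only a possibility.
- **That such pre-dose abnormalities would also dilute the contrast.** Adding the same amount to both arms does not shrink the absolute difference. With assumed rates of 6% v 0%, adding 5 points to each gives 11% v 5%, a difference of 6 points both times.

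**Conclusion.** The point holds for on-drug values filed as baseline. For a patient first dosed before 48 h, any safety sample between first dose and 48 h counts as baseline. A new abnormality in that sample can drop out of the normal-to-significant cell and, depending on the unstated rule for several values, out of its denominator. This conflicts with the first-dose reference for adverse events and lacks the safeguard given to TCD and HP/MDA.

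No figure in the SAP changes. The fall from 20.0% to between 15.8% and 5.9% for k = 2 to 6 illustrates the mechanism under assumed counts and is not an estimate for this trial. The actual size depends on the safety sampling times and the distribution of time from ictus to first dose, neither of which is given. The change is worth making because it removes a possible bias against detecting an early drug effect in a display that serves a primary objective. Safety conclusions do not rest on this table alone.

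**What to change.** Set the row by the clinical significance of the last value before first dose, with a separate row for patients with no pre-dose value. Set the column by any clinically significant value after first dose. State how a sample taken on the day of first dose is classed where only dates exist. Apply this to blood and urine, and use the same baseline for the change-from-baseline summaries and box-plots.

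If many patients lack a pre-dose sample, keep the 48 h row but split it by arm into values taken before and after first dose, in line with the TCD and HP/MDA summaries, and say which value counts when there are several.

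The cost is SAP wording and programming. Section 7 (Qualifying Evaluations) lists the date and time of dosing, but the SAP does not confirm that laboratory sample times are recorded, hence the same-day rule. The main drawback is that some patients, possibly many, will have no pre-dose value. That number should be counted before the tables are finalised and while the data are still blinded.
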